### Outcome measures

The primary outcome is the change in energy intake at 12 weeks. Participants with T2DM who are recruited to similar trials typically have a mean weight of 85–95 kg and are sedentary or minimally physically active with an expected daily energy expenditure of 1780–2100 kcal. The energy loss secondary to dapagliflozin treatment is 300 kcal/day, and the placebo-subtracted weight loss is 1.5–2 kg equivalent to ∼62–83 kcal/day. Thus, the expected compensatory increase in energy intake is ∼220–240 kcal/day. Accounting for the osmotic diuresis and 10% compensatory increase as a result of this, this would further increase to ∼240–260 kcal/day (12.5–13.4% of intake).

### Sample size

The primary outcome measure is energy intake after 12 weeks. On the basis of previous research,^12^ we estimate that 52 participants are required in order to detect a change in energy intake of 12.5% with 80% power and at a two-sided 5% level of significance. This estimate is based on a correlation between measurements of 0.7 and a between-participant SD of 165, both of which are based on a previous trial.^12^ The change in energy intake of 12.5% is based on a baseline consumption of 460 g in the test meal (ie, a 12.5% change equates to a change of 57.5 g). This calculation incorporates an allowance for participant dropout of 20%. The estimate was calculated using *PROC POWER* in SAS V.9.3 and is based on the paired *t*-test.

The study is not formally powered to detect differences in liver or visceral fat, but in a previous study we were able to detect a clear reduction or 7–11% of subcutaneous and visceral adipose tissue and a reduction in liver fat of 42% (IQR: −59.3 to −16.5%) with GLP-1 analogue treatment on a study of n=25 in a pre-post treatment analysis.^11^

Recruitment will take place over 12 months and will take place in Aintree University Hospital, Liverpool, UK (four to five patients per month). Participants will be recruited either from existing databases of volunteer patients, diabetes clinics in the hospital and community and by advertisement in the local press. The randomisation for each stratum will be performed within balanced blocks to ensure approximately equal numbers of participants across the treatment sequences within each stratum. The randomisation will be performed in two strata, female and male participants.

### Screening, enrolment and randomisation

After giving written informed consent, potentially eligible participants will attend a screening visit within 6 weeks prior to randomisation; this includes a medical history to confirm the participant's eligibility to participate as determined by the inclusion/exclusion criteria, physical examination, blood tests, urinalysis and an ECG. A decision as to the participant's eligibility will be made once all the results are available. The number and size of tablets will be identical for the investigational products (dapagliflozin 10 mg and placebo) for the four treatment sequences.

### Dosage and administration of study treatments

Participants will be instructed to take a tablet with water (dapagliflozin 10 mg or matching placebo) each morning for the duration of the study (26 weeks) while continuing with their other usual medication and to attend for scheduled study visits. Participants will be asked to return all unused investigational products, including any empty packages to the study pharmacy at each visit. The participant's compliance will be discussed at each study visit and assessed based on returned tablet counts.

### Study visits and procedures

#### Test meal visits (visits 1, 3, 5, 9 and 13)

These will take place at baseline, after 7 days and 14 days, 14 weeks and 26 weeks of treatment (tables 1 and 2). On visit 1, participants will be asked to attend the investigational unit at 8:00, having had nothing to eat or drink other than water from midnight. To keep study procedures identical for all test days, participants will then be asked to take a dose of (single blind) placebo tablet. Participants will be weighed and their pulse and blood pressure recorded. An explanation and demonstration of Visual Analogue Scale (VAS) questionnaires, universal eating monitor (UEM) and ventilated hood will be given.

**Table 1 BMJOPEN2016013539TB1:** Study procedures

Time point guidelines	Procedure
Arrival 8:30	7 mL blood sample taken (visit 9 only)
	Placebo tablet taken
	Weight, pulse and blood pressure taken. Participants asked to empty bladder and start of timed urine collection
08:40	Basal metabolic rate measurement (indirect calorimetry—see below for details)
08:50	Participants will complete a series of pre-breakfast VAS ratings to measure hunger and other subjective variables
09:00	Participants will be provided with a fixed-quantity breakfast, consisting of cornflakes with milk, toast and preserve, tea/coffee and orange juice
10:00, 11:00, 12:00 (first one followed by 3 every hour)	Participants will complete the same set of VAS ratings as used pre-breakfast, providing a premeal set of ratings
10:00	Indirect calorimetry
11:00	Indirect calorimetry
12:00	Indirect calorimetry
13:00	Participants will be given a test meal in the UEM laboratory. The meal consists of a pasta dish with tomato sauce, and participants may eat ad lib and signal when they have finished the meal. The UEM will continuously monitor decreases in food as it is consumed and will provide a continuous record of food consumption throughout the meal
14:00, 15:00, 16:00, 17:00 (1st one followed by 3 every hour)	Participants will complete the same set of VAS ratings as used pre-breakfast, providing a postmeal set of ratings
14:00	Indirect calorimetry
15:00	Indirect calorimetry
16:00	Indirect calorimetry

UEM, universal eating monitor; VAS, Visual Analogue Scale.

**Table 2 BMJOPEN2016013539TB2:** Assessments and procedures during screening and study visits

Procedure	D −21 to −2	D 0	D 5–6	D 7	D 12–13	D 14	W 6	W 10	W 13–14	W 14	W 18	W 22	W 25–26	W 26
Visit	0	1	2	3	4	5	6	7	8	9	10	11	12	13
Informed consent	X													
Physical examination	X									X				X
Fasting visit		X		X		X				X			X	X
Bloods	X									X				X
Pregnancy test	X													
Urinalysis	X													X
Height	X													
Weight	X			X		X				X				X
BP, pulse	X			X		X								X
ECG	X													X
Glucometer provision and training	X													
Drug dispensing	X	X		X		X				X				
Drug administration				X		X	X	X	X	X	X	X	X	X
AE reporting				X		X	X	X	X	X	X	X		X
Con-med check	X			X		X	X	X	X	X	X	X		X
Compliance check				X		X	X	X	X	X	X	X		X
8 hour urine		X		X		X				X				X
Telephone reminder		X					X	X			X	X		
Test meal		X		X		X				X				X
TFEQ	X													X
fMRI	X		X		X				X				X	
MR/MRS	X								X				X	

AE, adverse event; BP, blood pressure; D, day; fMRI, functional MRI; MRS, magnetic resonance spectroscopy; TFEQ, three factor eating quotient; W, week.

This procedure will be followed on additional test days (visits 2, 6 and 10). Drug/placebo administration will take place before the fixed breakfast is consumed on each occasion.

##### Food intake and eating behaviour

Food intake and within meal assessment of hunger, fullness, desire to eat and prospective consumption will be collected using the Sussex Ingestion Pattern Monitor (SIPM V.2.0.13, University of Sussex), which comprises a concealed digital balance linked to a computer system. This system is similar to the UEM and allows continuous recording of food intake throughout a meal as well as custom programming for presentation of digital VASs pre-meal and post-meal, and at set intervals during the meal (every 150 g). Using this technology not only offers accurate collection of cumulative intake data, but also records data on subjective within meal measures of satiation. The assessment of within meal measures of satiation provides a behavioural correlate of satiety processes during a meal.^13^ Thus, the mechanisms by which potential increases in intake occur can be characterised; for example, intake may be increased due to weakened within meal satiation/delayed development of satiety. Eating rate during the meal can also be assessed using SIPM, as well as meal duration, satiety quotient and ratings of palatability, providing essential information about drug effects on the microstructure of eating. Pen and paper VAS measures of appetite (hunger, fullness, desire to eat, prospective consumption, satisfaction, thirst and nausea) fluctuations throughout the day will also be collected allowing analysis of drug effects on satiety between meals. Taken together these data fully characterise drug effects on appetite and eating behaviour. All intake, appetite and eating behaviour measurements are taken at baseline, 7 days, 14 days, 14 weeks and 26 weeks.

##### Indirect calorimetry

Energy expenditure, resting metabolic rate (RMR) and RQ will be measured by indirect calorimetry data using a ventilated hood system and derived using the Weir equation.^14^
^15^ Measurements will be started after 5 min and performed for a 20 min period prior to the test meal and at 60, 120, 180 and 240 min postprandially. The first 5 min of each measurement will be discarded to allow for complete acclimatisation to the hood and the recumbent position, so that participants will have reclined for 10 min prior to any measurements being recorded for analysis. Urinary nitrogen excretion will be estimated by collecting all urine produced over the eight-hour period of observation in the laboratory and multiplying by a factor of 3 to approximate 24-hour urinary nitrogen excretion. Urine glucose excretion will also be measured over the same time period.

#### Imaging visits (visits 0, 2, 4, 8, 12)

Participants will be asked to attend the MRI unit on a separate day to the test meal; baseline measurements will be taken after screening and no more than 1 week before baseline test meal; other visits should take place within 1 week before or after the relevant test meal (for the week 24 visit this should be in the week preceding the final study visit/meal).

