**Trial registration number:**

ISRCTN14818531. EUDRACT number 2013-004264-60.

Strengths and limitations of this studyThis is the first study to address the discrepancy between the estimated and actual weight loss as a result of SGLT2 inhibition in a prospective within participant study design incorporating short-term and long-term effects.The study is designed to assess macrostructure and microstructure of eating behaviour and the use of imaging modalities provide a neurophysiological and mechanical correlate.The sample size is relatively small, although provides sufficient power to answer the primary research question.The measurement of energy expenditure is performed using indirect calorimetry as opposed to the gold standard whole body calorimetry.There may be a carryover effect on body weight and body composition changes since there is no wash-out period between the long-term cross over, but any effect of this on the primary outcome (food intake) should be minimal.

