##### Neural response to food cues (fMRI)

BOLD response to food images is assessed using a 3.0 Tesla Siemens Trio scanner (Siemens, Erlangen, Germany). Participants view sets of images of high calorie (hedonic) foods, low calorie (non-hedonic) foods and non-food control objects, in a fasted state, then again 1 and 3 hours after consuming a fixed load breakfast. This is conducted to understand drug effects on the central mechanisms underpinning eating behaviour. The brain areas of interest are defined as hypothalamus, lingular gyrus, posterior insula, anterior cingulate gyrus, pre-central gyrus, posterior cingulate gyrus, middle frontal gyrus and lateral orbitofrontal cortex. Activation in areas of the brain involved in regulatory/homeostatic control of appetite (insula/hypothalamus) can be assessed on and off drug, in different states of satiety and over time. Furthermore, this design allows for observation of drug-related changes to reward neurocircuitry in response to hedonic versus non-hedonic food images. Neural pathways associated with reward-related behaviour and motivation to consume interact with homeostatic brain regions to control appetite and energy balance, thus fMRI data can provide a neurophysiological correlate of drug effects on food reward and homeostatic hunger.^16^ These measurements will be made at baseline, and at 5 or 6 days, 12 or 13 days and at 13–14 and 25–26 weeks (before the test meal evaluations). MR images will be imported into Statistical Parametric Mapping software (SPM12) for processing, followed by statistical analysis to test for significant regional BOLD response change. Following the fMRI session in the fasted state trial participants will be provided with breakfast.

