##### Liver fat by MRS and body fat volume by MRI (visit 0, 8, 12)

These measurements will be made at baseline, and at 14 and 26 weeks. Proton magnetic resonance spectroscopy of the liver will be performed as previously described.^11^ Three voxels of interest will be identified in the liver standard sites avoiding ducts and vasculature. In liver, voxel placement in post-treatment studies will be guided by reference to the pretreatment images. ^1^H MR spectra will be quantified using the AMARES algorithm in the software package jMRUI V.3.0. Intrahepatocellular lipid content (IHCL) is expressed as percentage of CH2 lipid signal amplitude relative to water signal amplitude after correcting for T1 and T2.^17^ Fat quantification by ^1^H-MRS has been validated against gold standard biochemical measurements.^18^ The mean interexamination coefficient of variation (CoV) for using this protocol is 7% (range 4–12%), and the mean intraexamination CoV is 6%.^17^

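### The general imaging window allows scans at visits 2, 4 and 8 after the treatment switch, contradicting the fMRI section and Table 2

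*Protocol article*

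**What the plan says.** The section on imaging visits sends participants to the MRI unit on a day other than the test-meal day. For imaging after baseline it states that "other visits should take place within 1 week before or after the relevant test meal". It makes one exception: "for the week 24 visit this should be in the week preceding the final study visit/meal".

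Two other places give a different timing:

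- The fMRI section puts the scans "at 5 or 6 days, 12 or 13 days and at 13–14 and 25–26 weeks (before the test meal evaluations").
- Table 2 ("Assessments and procedures during screening and study visits") lists imaging visits 2, 4, 8 and 12 at days 5–6, days 12–13, weeks 13–14 and weeks 25–26. Each precedes its paired meal visit (3, 5, 9 and 13 at day 7, day 14, week 14 and week 26).

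For liver fat and body fat, the MRS/MRI section gives only the nominal times: "These measurements will be made at baseline, and at 14 and 26 weeks". It does not say whether the scan precedes or follows the meal.

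On meals and dosing, the test-meal section says "These will take place at baseline, after 7 days and 14 days, 14 weeks and 26 weeks of treatment". Tablets are taken "each morning for the duration of the study (26 weeks"). The strengths and limitations list adds that "there is no wash-out period between the long-term cross over".

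**The concern.** A 7-day treatment period combined with a scan window of one week either side of the meal cannot guarantee that the scan is taken on the treatment under which it will be analysed. The same applies, more weakly, at the week-14 switch. Because the last visit alone is restricted to before its meal, the post-meal allowance reads as intended for visits 2, 4 and 8, so staff following that sentence could book scans at times the fMRI section rules out.

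The BOLD response after 7 days and 12 weeks, VAT and SAT at 12 weeks, and liver fat are all named secondary objectives. A scan taken after the switch but labelled with the treatment just finished pulls the treatment contrast towards zero. The intended on-treatment measurement cannot be recovered later.

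**Working it through.** **Is a post-meal scan a post-switch scan?** The periods are 7 days, 7 days, 12 weeks and 12 weeks: 1 + 1 + 12 + 12 = 26 weeks, equal to the stated length of daily dosing, so there is no room for a gap. Table 2 lists drug dispensing at days 0, 7 and 14 and week 14, so the next supply is issued at the meal visit. No wash-out is stated for the long-term crossover; for the short-term switches it is inferred from this arithmetic.

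**Days allowed by the imaging-visit section.** Take the meal day plus or minus 7 days and remove test-meal days (0, 7, 14, 98, 182), because imaging must be on a separate day.

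| Visit | Meal | Allowed before meal | Allowed after meal | Table 2 |
|---|---|---|---|---|
| 2 | D7 | D1–6 | D8–13 (second 7-day period) | D5–6 |
| 4 | D14 | D8–13 | D15–21 (first 12-week period) | D12–13 |
| 8 | W14 (D98) | D91–97 | D99–105, to W15 (second 12-week period) | W13–14 |
| 12 | W26 (D182) | D175–181 | none | W25–26 |

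Roughly half the allowed days at visits 2, 4 and 8 lie in the next period. fMRI is exposed at all three visits; liver fat, VAT and SAT are exposed at visit 8 only.

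**Does the drug change at each switch?** There are four sequences, and figure 2 is not shown. Assume ABAB, ABBA, BAAB and BABA in equal numbers. The drug then changes after day 7 and after week 14 in all four, but after day 14 in only two (ABAB and BABA).

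**Illustrative dilution.** Let *f* be the share of late scans at each exposed visit, and assume that BOLD follows the current drug at once (worst case). Score a scan +1 if taken on its labelled treatment and −1 if on the other; the contrast retained is the mean expected score of the two scans.

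- Visit 2: (1 − f) − f = 1 − 2f.
- Visit 4: the average of 1 − 2f (two sequences) and 1 (two sequences) = 1 − f.
- 7-day contrast: [(1 − 2f) + (1 − f)]/2 = 1 − 1.5f.
- Visit 8: 1 − 2f. Visit 12: 1. 12-week contrast: [(1 − 2f) + 1]/2 = 1 − f.

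| f | 7-day contrast retained | 12-week contrast retained |
|---|---|---|
| 0.10 | 0.85 | 0.90 |
| 0.25 | 0.625 | 0.75 |
| 0.50 | 0.25 | 0.50 |

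For fat measures, a late visit 8 scan follows 12 weeks on the labelled drug and at most 1 week on the other, so the immediate-response formula does not apply and the dilution is much smaller.

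**Sample size.** The stated N reproduces: SD of the paired difference = 165 × √(2 × (1 − 0.7)) = 127.8 g; a paired t-test for 57.5 g at 80% power and two-sided 5% needs 41; 41/0.8 = 51.25, rounded up to 52. It rests on test-meal intake and does not involve imaging.

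**The case against.** The best defence is that two specific statements outweigh one loose one. The fMRI section requires scanning before the meal, Table 2 orders every imaging visit ahead of its meal, and the sentence with the wide window also misnames the last visit's week. On that view post-switch scanning was never the plan. This stands in part: the defect is an inconsistency, and a reader should not infer that the protocol settles on scanning after the switch. But the exception for the last visit gives the post-meal allowance a deliberate look, and for liver fat and body fat the dedicated section does not say that the scan comes before the meal.

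Stronger readings are tempting and are not supported:

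- That visit 2 could be scanned on day 0 before any drug, or visit 4 on day 7 under the previous treatment. Both are test-meal days, which the imaging section excludes.
- That every late scan is on the other drug. At day 14 this probably holds in only some sequences.
- That the contrasts would reverse. For one participant's 7-day pair, that needs both scans late in a sequence that changes drug at day 14. The 12-week pair cannot reverse in this way, because visit 12 is restricted.
- That a particular loss can be expected. The document gives no share of late scans.

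**Conclusion.** The point holds as an internal contradiction with a real consequence. Read as written, the imaging-visit section permits scans at visits 2, 4 and 8 in the next treatment period, while the fMRI section (for fMRI) and Table 2 (for all imaging) place them before the meal. The week 24 label for the last visit also disagrees with weeks 25–26 in Table 2.

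The size of the harm is unknown. It depends on how many scans are late, how quickly BOLD responds and the sequences in figure 2; the tabulated dilutions are worst-case illustrations, not estimates. The effect on week-14 fat measures would be small. A reader might infer that the trial's main conclusion is at risk; it is not, because test-meal intake and N = 52 do not depend on imaging dates. This should be fixed, but it concerns secondary imaging outcomes only.

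**What to change.** In the imaging-visit section, delete the allowance for scanning after the meal. Use the windows already in Table 2 and, for fMRI, in the fMRI section: days 5–6, days 12–13, weeks 13–14 and weeks 25–26, always before that period's test meal and before the switch. State the same for liver fat and body fat, and correct week 24 to agree with Table 2.

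Treat a scan not obtained before the switch as missing for that period. The planned mixed model can use the participant's remaining data, under its usual missing-at-random assumption. Do not relabel body-fat scans by the drug being taken on the scan date: a scan a few days after week 14 mainly reflects the preceding 12 weeks, so relabelling would create a worse misclassification than the one it removes.

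The cost is a short text change in the protocol and any imaging instructions, and a few scans that become missing instead of late. With the change, no scan can be credited to the wrong period, and N is unchanged.

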##### Neural response to food cues (fMRI)

BOLD response to food images is assessed using a 3.0 Tesla Siemens Trio scanner (Siemens, Erlangen, Germany). Participants view sets of images of high calorie (hedonic) foods, low calorie (non-hedonic) foods and non-food control objects, in a fasted state, then again 1 and 3 hours after consuming a fixed load breakfast. This is conducted to understand drug effects on the central mechanisms underpinning eating behaviour. The brain areas of interest are defined as hypothalamus, lingular gyrus, posterior insula, anterior cingulate gyrus, pre-central gyrus, posterior cingulate gyrus, middle frontal gyrus and lateral orbitofrontal cortex. Activation in areas of the brain involved in regulatory/homeostatic control of appetite (insula/hypothalamus) can be assessed on and off drug, in different states of satiety and over time. Furthermore, this design allows for observation of drug-related changes to reward neurocircuitry in response to hedonic versus non-hedonic food images. Neural pathways associated with reward-related behaviour and motivation to consume interact with homeostatic brain regions to control appetite and energy balance, thus fMRI data can provide a neurophysiological correlate of drug effects on food reward and homeostatic hunger.^16^ These measurements will be made at baseline, and at 5 or 6 days, 12 or 13 days and at 13–14 and 25–26 weeks (before the test meal evaluations). MR images will be imported into Statistical Parametric Mapping software (SPM12) for processing, followed by statistical analysis to test for significant regional BOLD response change. Following the fMRI session in the fasted state trial participants will be provided with breakfast.

##### Body composition

Participants will undergo MR whole body scanning in a 1.5 T Siemens Symphony scanner (Siemens Medical Solutions, Erlangen, Germany) at a single site, the University of Liverpool Magnetic Resonance and Image Analysis Research Centre, as previously described.

##### Liver fat by MRS and body fat volume by MRI (visit 0, 8, 12)

These measurements will be made at baseline, and at 14 and 26 weeks. Proton magnetic resonance spectroscopy of the liver will be performed as previously described.^11^ Three voxels of interest will be identified in the liver standard sites avoiding ducts and vasculature. In liver, voxel placement in post-treatment studies will be guided by reference to the pretreatment images. ^1^H MR spectra will be quantified using the AMARES algorithm in the software package jMRUI V.3.0. Intrahepatocellular lipid content (IHCL) is expressed as percentage of CH2 lipid signal amplitude relative to water signal amplitude after correcting for T1 and T2.^17^ Fat quantification by ^1^H-MRS has been validated against gold standard biochemical measurements.^18^ The mean interexamination coefficient of variation (CoV) for using this protocol is 7% (range 4–12%), and the mean intraexamination CoV is 6%.^17^

